### Outcome Measures

Renal function markers will comprise serum creatinine, urea, blood urea nitrogen, and uric acid, which are biomarkers widely used in the clinical follow-up of kidney transplant recipients [24,25]. Estimated glomerular filtration rate will be calculated using the Chronic Kidney Disease Epidemiology Collaboration equation based on serum creatinine values, age, and sex. For inferential analysis, serum creatinine will be the prespecified hierarchical primary renal end point. It is acknowledged that resistance training may increase skeletal muscle mass, which could influence serum creatinine levels independently of renal function.

Metabolic health will be assessed through fasting glucose, total cholesterol, HDL-C, low-density lipoprotein cholesterol, and triglycerides. HDL-C will be the prespecified primary metabolic marker because of its sensitivity to exercise-induced adaptations and its clinical relevance in cardiovascular risk reduction.

Secondary outcomes will include clinical, anthropometric, body composition, physical fitness, and neuromuscular function variables. A predefined analytic hierarchy will be established, prioritizing renal function (serum creatinine) as the primary outcome, followed by metabolic health indicators (HDL-C) and secondary outcomes related to physical performance and cardiovascular risk.

### Instruments and Procedures

Assessments will be performed at 2 time points, baseline (preintervention assessment) and after completion of the 12-week intervention (postintervention assessment), by trained evaluators blinded to group allocation, following standardized protocols to ensure the validity, reliability, and reproducibility of the measurements.

Primary outcomes will be evaluated through venous blood analysis processed at a certified clinical laboratory (Instituto de Diagnóstico Médico). Samples will be collected between 6 AM and 9 AM by specialized nursing staff under standardized conditions, including a minimum 12-hour fasting period and abstention from physical exercise for 24 hours prior to sampling [26].

Blood pressure will be measured using a validated digital sphygmomanometer, following standardized protocols with participants seated and at rest for at least 5 minutes [27]. Waist and hip circumferences will be assessed using a nonelastic anthropometric tape according to International Society for the Advancement of Kinanthropometry protocols and will be used along with biochemical markers to diagnose metabolic syndrome according to the National Cholesterol Education Program Adult Treatment Panel III criteria [27,28]. All anthropometric measurements will be conducted by evaluators certified under International Society for the Advancement of Kinanthropometry standards, and both intrarater and interrater technical errors of measurement will be calculated to ensure data quality and reliability. Additionally, a metabolic risk index will be calculated by transforming metabolic variables into standardized scores using previously validated methodologies [29].

Body composition will be assessed using segmental bioelectrical impedance analysis (Tanita Corp), allowing estimation of body mass, muscle mass, and body fat percentage [30]. Height will be measured using a digital stadiometer following standardized anthropometric protocols.

Muscle strength will be assessed using handgrip dynamometry with a validated digital dynamometer (Takei Scientific Instruments Co Ltd), recording the highest value obtained from maximal attempts [31]. Functional strength will also be evaluated using push-up and horizontal jump tests, which are used as indicators of global neuromuscular performance [32]. A general strength index will be calculated by integrating standardized scores (*Z* scores) from these tests.

The force-velocity profile will be assessed using a validated linear encoder (T-Force System; Ergotech), a device widely used to quantify mean propulsive velocity and estimate neuromuscular profiles during resistance exercises [33]. The assessment will be conducted using a Smith machine and will include bench press, shoulder press, and half squat exercises. The eccentric phase will be performed at a controlled velocity (approximately 0.50-0.65 m/s), and the concentric phase will be performed at maximal intended velocity. The load will be progressively increased until the mean propulsive velocity is <0.8 m/s. This procedure has demonstrated high validity and reliability [18,33].

Physical activity level will be assessed using the International Physical Activity Questionnaire, and perceived physical fitness will be assessed using the International Fitness Scale, both validated in Colombian populations [34,35].

### Intervention: Training Protocols

The VBT program will be conducted over 12 weeks, with 3 weekly sessions on nonconsecutive days, totaling 36 sessions. Each session will last approximately 50 to 80 minutes and will include warm-up, main training, and cool-down phases. Exercises will include bench press, half squat, and military press, performed on a Smith machine, with velocity monitored using a linear encoder.

Participants will be randomly assigned to 1 of 2 intervention groups. Group A—maximal velocity with velocity loss control: participants will perform the concentric phase at maximal voluntary velocity and the eccentric phase in a controlled manner. Sets will be terminated when mean propulsive velocity decreases by 20% relative to the fastest repetition in the set. The load will be progressively increased following the principle of progressive overload. The detailed load progression and training parameters for the maximal velocity group are presented in Table 1.

**Table 1 table1:** Load progression and training parameters for the maximal velocity group.

Sessions	Intensity (% 1-repetition maximum)	Sets per exercise	Termination criterion (% velocity loss)	Rest between sets (minutes)	Rest between exercises (minutes)
1-6	20	2	20	1	3
7-12	30	2	20	1	3
13-18	40	3	20	2	3
19-24	50	3	20	2	3
25-36	60	4	20	2	3

Group B—constant submaximal velocity training: participants in this group will perform the same exercises, with identical load progression, number of sets, and recovery periods. However, repetitions will be performed at a concentric velocity equivalent to 50% of the previously determined individual maximal velocity, eliminating the relative velocity loss criterion as the indicator for set termination. In this group, training volume will be standardized using a fixed number of repetitions per set. The detailed load progression and training parameters for the maximal velocity group are presented in Table 2.

**Table 2 table2:** Load progression and training parameters for the constant submaximal velocity group.

Sessions	Intensity (% 1-repetition maximum)	Repetitions per set	Sets per exercise	Rest between sets (minutes)	Rest between exercises (minutes)
1-6	20	30	2	1	3
7-12	30	25	2	1	3
13-18	40	20	3	2	3
19-24	50	18	3	2	3
25-36	60	15	4	2	3

All training sessions will be supervised by a professional in sports sciences with experience in resistance training and clinical rehabilitation, who will ensure proper exercise execution and compliance with the established protocol. During each session, mean propulsive velocity, external load, number of repetitions, number of sets, and program adherence will be recorded using a linear encoder and a digital monitoring system. This approach will ensure proper implementation of the intervention, optimize individualized load prescription, and guarantee participant safety.

At the end of each session, a cool-down period of approximately 10 minutes will be performed, including static stretching exercises targeting the main muscle groups involved, such as the pectorals, deltoids, quadriceps, hamstrings, and gluteal muscles, to facilitate neuromuscular recovery and reduce injury risk. Adherence to the program will be defined as attendance ≥85% of the scheduled sessions, and any adverse events will be documented and evaluated by the research team. The protocol has been designed according to international recommendations for resistance training in clinical populations, ensuring appropriate conditions of safety, progression, and individualization of training [7,16,19].

### Safety Monitoring

Adverse events will be continuously monitored throughout the intervention by the research team. Any exercise-related complication or abnormal clinical response will be documented and evaluated. Given the low-risk nature of the intervention and the pilot design of the study, a formal data monitoring committee has not been established. However, safety oversight will be conducted by the principal investigator and the clinical collaborators. Criteria for discontinuation will include any medical condition that contraindicates continued participation in the intervention.

### Data Management

All study data will be recorded in a secure digital database with restricted access. Data entry will be verified through double-check procedures, and periodic quality-control checks will be performed to ensure accuracy, consistency, and completeness of the dataset. Participant information will be coded to preserve confidentiality throughout data management and analysis.

### Statistical Analysis

Analyses will be conducted according to the intention-to-treat principle, including all participants according to their assigned group. Missing data will be handled using appropriate imputation methods, and sensitivity analyses will be conducted to assess the robustness of the results. Continuous variables will be expressed as mean and SD (or median and IQR when normality assumptions are not met), and categorical variables will be expressed as frequencies and percentages. Normality of the data will be assessed using the Shapiro-Wilk test and graphical inspection of residuals. A statistical significance level of *P*<.05 will be considered, and 95% CI will be reported. The effect of the intervention will be primarily analyzed using an analysis of covariance model, using the postintervention value as the dependent variable, group as a fixed factor, and baseline value as a covariate, to adjust for potential baseline differences and improve estimator precision. As a complementary analysis, and to appropriately account for the longitudinal structure of the data, linear mixed-effects models will be used with fixed effects for group, time (before and after), and the group×time interaction, including a random intercept for each participant. Given that the study will include 2 primary outcomes (renal function and metabolic health), a predefined analytic hierarchy will be applied, with renal function evaluated first using serum creatinine, followed by metabolic health markers, particularly HDL-C, to control the type I error rate. Categorical variables, such as the presence of metabolic syndrome, will be compared between groups using the Fisher exact test. Effect size will be estimated using Cohen *d*, and its magnitude will be interpreted as trivial (<0.2), small (0.2-0.59), moderate (0.60-1.19), large (1.2-2.0), or very large (>2.0), according to established criteria [36]. All statistical analyses will be performed using SPSS (version 23; IBM Corp).

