## Methods

### Study Design

This study is designed as a pilot randomized, parallel-group controlled clinical trial with a 1:1 allocation ratio to assess the feasibility, safety, and preliminary efficacy of 2 VBT strategies in kidney transplant recipients. The pilot nature of the trial aims to generate preliminary estimates of effect size and variability to inform future adequately powered randomized controlled trials in this population. The protocol has been developed in accordance with the SPIRIT (Standard Protocol Items: Recommendations for Interventional Trials) guidelines to ensure methodological rigor, transparency, and reproducibility [22]. A completed SPIRIT 2025 checklist is provided as Multimedia Appendix 1.

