### Sample Size

The sample size was estimated based on the primary outcome domains of the study, corresponding to renal function and metabolic health, specifically changes in serum creatinine and HDL-C. The calculation was informed by evidence from previous supervised exercise interventions in kidney transplant recipients that reported clinically meaningful changes in these physiological parameters [10,16,23]. Considering the exploratory nature of this pilot trial, the sample size was not primarily determined to test hypotheses or detect statistically significant between-group differences. Rather, a pragmatic approach was adopted to include 14 participants (7 participants per group), which was considered sufficient to evaluate key feasibility outcomes, such as recruitment, adherence, retention, and safety, as well as to provide preliminary estimates of variability and effect size. These estimates are intended to inform the design and sample size calculation of a future fully powered randomized controlled trial. Therefore, any between-group comparisons conducted in this study will be considered exploratory and interpreted with caution. The calculation was performed using the Power and Sample Size Calculation software (Vanderbilt University).

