### Randomization and Allocation Concealment

Participants will be assigned to intervention groups using a block randomization procedure with a 1:1 allocation ratio, generated through a computerized random sequence generator. To ensure allocation concealment, a centralized online randomization platform (Research Randomizer, Social Psychology Network) will be used, to which only the methodological coordinator will have access. This coordinator will not be involved in outcome assessment or data analysis. After eligibility criteria are confirmed, informed consent is obtained, and baseline assessments are completed. Participant information will be entered into the platform, which automatically assigns participants to 1 of the 2 intervention groups using an encrypted system, ensuring allocation unpredictability and minimizing selection bias.

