## Results

The study was approved by the Research Ethics Committee of Fundación Universitaria del Área Andina (approval 15, dated April 22, 2025) and prospectively registered at ClinicalTrials.gov (NCT07370727). The study was initiated in September 2025. Participant recruitment and the intervention phase have been completed. All 14 participants completed the 12-week training program, and no participants were lost to follow-up. Preintervention and postintervention data collection were completed according to the study protocol. The study database has been cleaned and locked, and statistical analyses are currently underway. Publication of the primary study results is anticipated in late 2026.

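### The Cohen d magnitude labels are read from the point estimate; with 7 per arm, a pooled-SD between-group d is labelled non-trivial in about 71% of comparisons with no true difference

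*Protocol article*

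**What the plan says.** The protocol article, Statistical Analysis, states the rule as "Effect size will be estimated using Cohen *d*, and its magnitude will be interpreted as trivial (<0.2), small (0.2-0.59), moderate (0.60-1.19", and continues with large (1.2-2.0) and very large (>2.0). The only input to this scale is the value of d. Every d receives a category, and none of the categories means that the data cannot tell.

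The same section sets a 5% significance level and says that 95% CIs will be reported, without attaching an interval to d or making the label depend on one. The main analysis is an ANCOVA of the post-intervention value adjusted for baseline.

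Two other places bear on how the labels would be used. Study Design says that the pilot is meant to "generate preliminary estimates of effect size and variability to inform future adequately powered randomized controlled trials in this population". Sample Size says that "any between-group comparisons conducted in this study will be considered exploratory and interpreted with caution".

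**The concern.** A magnitude scale is informative only if the estimate is precise relative to the width of its bands. The bands here start at 0.2 and 0.6. With 7 per arm, sampling error alone moves d by about half a unit, so chance differences will usually land in a named, non-trivial band.

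Followed as written, the rule would lead the results paper to describe chance differences in creatinine, HDL-C or a secondary outcome as a small or moderate effect. A reader would take this as a statement about one velocity strategy against the other. The general call for caution does not change which word is assigned.

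**Working it through.** **Inputs from the protocol article**
- Planned size: "a pragmatic approach was adopted to include 14 participants (7 participants per group" (Sample Size), with 1:1 allocation (Randomization and Allocation Concealment).
- Analysed: "All 14 participants completed the 12-week training program, and no participants were lost to follow-up" (Results), so 7 against 7 and 12 degrees of freedom for a pooled SD.
- Cut-offs 0.2, 0.6, 1.2 and 2.0 (Statistical Analysis).

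The article states no error rate or precision for the labels, so there is no figure of its own to reproduce first.

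**Assumptions, not in the article:** d is a between-group difference over the pooled SD; data are normal with equal SDs; the true difference is zero.

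**Step 1. Spread of d.** d = t × √(1/7 + 1/7), with t on 12 df. √(2/7) = 0.5345, which is 0.5345/0.2 = 2.7 times the trivial limit.

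**Step 2. Chance of each label with no true difference.** P(|d| ≥ c) = 2 × P(t₁₂ ≥ c/0.5345).

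| Cut-off c | c/0.5345 | P(\|d\| ≥ c) |
|---|---|---|
| 0.2 | 0.374 | 0.715 |
| 0.6 | 1.122 | 0.284 |
| 1.2 | 2.245 | 0.044 |

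Non-trivial: about 71%. Small only: 0.715 − 0.284 = 0.431, about 43%. Moderate or larger: about 28%.

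**Step 3. Dependence on the standardizer** (simulation with no true difference).

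| Definition of d | P(non-trivial) |
|---|---|
| Post values over post SD | 71-72% |
| Change scores over SD of change | 72% |
| ANCOVA difference over residual SD | 72-73% |
| ANCOVA difference over raw SD, correlation 0.5 | 68-69% |
| same, 0.7 | 62% |
| same, 0.8 | 56% |
| same, 0.9 | 43% |

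The pre-post correlations are assumed. At 0.95 the last definition falls to 27%.

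**Step 4. What an observed d is compatible with** (exact 95% CI, inverting the noncentral t on 12 df).

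| Observed d | Label | 95% CI | Bands covered |
|---|---|---|---|
| 0.2 | small | −0.85 to 1.25 | moderate in the opposite direction to large |
| 0.6 | moderate | −0.49 to 1.66 | small in the opposite direction to large |
| 1.2 | large | 0.03 to 2.33 | trivial to very large |

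The CI excludes zero only from |d| = 2.179 × 0.5345 = 1.16. Every small label, and every moderate label below 1.16, therefore comes with an interval that includes zero.

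**Step 5. When there is a true effect.** At a true d of 0.4, in the middle of the small band, |d| falls in that band about 38% of the time, and with the correct sign about 28%. A non-trivial label in the wrong direction occurs about 13% of the time.

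**Step 6. Small-sample bias.** Plain d runs slightly high. The Hedges factor is 1 − 3/(4 × 12 − 1) = 0.936. With Hedges g, the non-trivial share under no difference falls only from 71% to 70%, so bias is a minor part of the problem.

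**The case against.** The strongest reply is that d is a descriptor added at the end of the section. Inference runs through the ANCOVA, with a significance level, CIs and a creatinine-then-HDL-C order, and a size label does not claim that an effect is real. This stands in part. The 71% is not the error rate of any decision that the plan states, and the plan's reporting as a whole is not blind to uncertainty: 95% CIs are promised, and both Sample Size and the Discussion ask for caution. But the article says that magnitude will be *interpreted* by the cut-offs, and neither the CI nor the caution alters the word that results.

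Three stronger readings are tempting, and the article does not support them:
- *Effect size is the trial's main deliverable.* Study Design lists feasibility, safety and preliminary efficacy together, the numeric success thresholds are for feasibility outcomes, and Sample Size justifies 14 participants first by these.
- *The labels will be carried into the next trial's design.* Sample Size carries forward numerical estimates of variability and effect size, not verbal categories.
- *71% is a fixed property of the plan.* It depends on a standardizer that the article does not give. If d were a within-group pre-post measure, the calculation for two identical regimens would not apply.

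The missing standardizer may be settled in a fuller document and is not a fault in itself. It only widens the range of the figure. The cut-offs are attributed to established criteria and are not disputed here; the complaint is about applying them to a point estimate this imprecise.

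**Conclusion.** The concern holds for the label rule and goes no further. With 7 per arm, normal data and no true difference, a between-group Cohen d on the pooled SD is called small or larger in about 71% of comparisons, with about 43% small and 28% moderate or larger. The range is about 71-73% with a change-score or residual SD, and about 43-69% for an ANCOVA-adjusted difference over a raw SD at assumed correlations of 0.9 to 0.5. Under all of these definitions, two equivalent strategies would often be described as differing by a named, non-trivial amount. The primary test, the planned CIs and the exploratory status of the comparisons are unaffected. The change is worth making because it alters what the results paper can say about one strategy against the other.

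**What to change.** In Statistical Analysis, replace the labelling sentence with wording to this effect: the between-group standardized effect will be reported as Hedges g with its 95% CI and a named standardizer (for example, the pooled baseline SD or the ANCOVA residual SD). Magnitude will be interpreted over the interval, by stating the range of categories and the signs that the CI covers. Where the CI includes zero, the difference will not be described as a small, moderate or large effect of one strategy over the other. Apply this to both primary and all secondary outcomes.

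A stricter rule, allowing a label only when the whole CI lies beyond 0.2 on one side, is not advised. It would need an observed |d| of about 1.41, so small and moderate could never be used, and a true d of 1.2 would earn a label only about 38% of the time.

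The cost is a few sentences of wording and no new data. The database is locked, but the article says that analyses are still underway, and the same rule applies to every outcome whatever its result. The change should be dated and reported as made after database lock. The downside is that most comparisons will be described as compatible with a wide range of effects, which is what 14 participants can support.

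### Cohen d is fixed as the effect size without being tied to the baseline-adjusted ANCOVA and without a small-sample correction, in a 14-participant pilot meant to supply effect sizes

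*Protocol article*

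**What the plan says.** Under Statistical Analysis, the protocol article's primary model is an ANCOVA "using the postintervention value as the dependent variable, group as a fixed factor, and baseline value as a covariate". The stated reason for the covariate is "to adjust for potential baseline differences and improve estimator precision".

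Later in the same paragraph: "Effect size will be estimated using Cohen" *d*. Five bands are then fixed for reading it, with limits at 0.2, 0.6, 1.2 and 2.0, running from trivial to very large. The paragraph does not say whether the numerator is the adjusted difference, the raw post-intervention difference or the difference in change. It does not name the SD in the denominator and mentions no small-sample correction. It does promise 95% CIs in general, and means and SDs (or medians and IQRs) for continuous variables.

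The effect size has a declared use. Study Design says the pilot "aims to generate preliminary estimates of effect size and variability to inform future adequately powered randomized controlled trials". Sample Size says "a pragmatic approach was adopted to include 14 participants (7 participants per group") and adds: "These estimates are intended to inform the design and sample size calculation of a future fully powered randomized controlled trial". Results reports: "All 14 participants completed the 12-week training program, and no participants were lost to follow-up".

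**The concern.** The plan adjusts for baseline because chance imbalance is likely with 7 per arm. It then names an effect size whose ordinary definition, the raw mean difference over the pooled SD, has no such adjustment. If that definition is used, the paper would carry two accounts of the same comparison that can differ in size and sometimes in direction.

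If *d* is instead taken from the ANCOVA output, a common denominator is the residual SD. That puts *d* on a different scale from between-participant variation, and the fixed bands were not adapted to it. In either form, *d* from so few participants overestimates the standardized effect on average.

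At stake is the number that the next trial's planners would pick up. The primary test is not at stake.

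**Working it through.** **Inputs.** From the article: 7 per arm and no losses, so the pooled SD has 14 − 2 = 12 df and the ANCOVA residual SD has 14 − 3 = 11 df; band limits 0.2, 0.6, 1.2 and 2.0. Assumed: normal data, equal baseline and post SDs, and a baseline-to-post correlation ρ of 0.5 to 0.9, because the article gives none. The article states no numerical effect size, SD or power, so it has no figure to reproduce.

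**1. Small-sample bias.** The exact Hedges factor is J(m) = Γ(m/2) / [√(m/2) · Γ((m−1)/2)].
- J(12) = 0.936; 1/0.936 = 1.068, so *d* is too large by 6.8% on average.
- J(11) = 0.930; 1/0.930 = 1.075, so 7.5%.

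For scale, the sampling SD of raw *d* with no true effect is √(12/10 × 2/7) = 0.59. At a true 0.5 the bias is about 0.5 × 0.068 = 0.03. In simulation, the correction alone moves *d* to another band in about 6–9% of trials. If a true 0.5 were carried forward inflated by 6.8%, a trial with 80% power and two-sided 5% alpha would be sized at 56 per arm instead of 63; for a true 0.8, 22 instead of 25. This shows the mean bias only; sampling error in *d* would dominate any real sizing.

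**2. Raw post-value *d* against the ANCOVA estimate.** With no true effect and the slope treated as known, the two differences have correlation √(1−ρ²), so they have opposite signs with probability arccos(√(1−ρ²))/π. Simulation (100,000 trials per setting, slope estimated) agrees:

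| ρ | Formula, no effect | Simulated, no effect | Simulated, true 0.5 SD |
|---|---|---|---|
| 0.5 | 16.7% | 17% | 10% |
| 0.7 | 24.7% | 25% | 14% |
| 0.8 | 29.5% | 30% | 16% |
| 0.9 | 35.6% | 36% | 17% |

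Illustration with invented values: baseline difference +0.10, post difference +0.05, slope 0.8, SD 0.20. Raw *d* = 0.05/0.20 = +0.25 (small). The adjusted difference is 0.05 − 0.8 × 0.10 = −0.03, which standardizes to −0.15 (trivial, opposite sign).

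Most disagreements are between inconclusive estimates. With no true effect, about 98% or more of them go with a non-significant ANCOVA, and in about 80% or more at least one of the two estimates is in the trivial band. A sign conflict together with a significant ANCOVA occurs in 0.2%, 0.4% and 0.8–0.9% of all trials at ρ = 0.7, 0.8 and 0.9 with no effect, and in 0.3%, 0.9% and 3.7–3.8% at a true 0.5 SD.

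**3. Precision.** With no true effect, the adjusted difference over the pooled baseline SD has sampling SD 0.44, 0.37 and 0.27 at ρ = 0.7, 0.8 and 0.9, against 0.59 for raw *d*. At ρ = 0.5 the gain is slight (0.54).

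**4. Residual-SD denominator.** The residual SD is σ√(1−ρ²), so *d* is multiplied by 1/√(1−ρ²): 1.15, 1.40, 1.67 and 2.29 at ρ = 0.5, 0.7, 0.8 and 0.9. Before small-sample bias, a true 0.5 (small) becomes 0.58, 0.70, 0.83 or 1.15. From ρ = 0.7 upward it is labelled moderate. With the bias added, it averages about 1.23–1.24 at ρ = 0.9, which is labelled large.

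**The case against.** The strongest reply is that the article never says *d* comes from raw post means. The ANCOVA is primary in the same paragraph, so *d* could equally be the standardized adjusted difference, whose sign cannot conflict with the ANCOVA. The choice of SD and of a Hedges factor is detail often left to an analysis plan, and a journal article is condensed. This stands in part: the sign reversal is a possibility that the wording leaves open, not something the plan states. It does not remove the point. The article itself selects Cohen *d*, fixes its bands and makes effect size a product of the pilot. As named, *d* is biased upward at this size, and its ordinary definition omits the adjustment that the plan asks for.

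A reader might also infer that the primary result would be self-contradictory, or the effect size unusable. The documents support neither. The primary result is the ANCOVA difference, the article calls between-group comparisons exploratory, and sign conflicts are mostly between near-zero estimates. Where means and SDs are published, a planner can usually restandardize.

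It is also fair that the 7% bias is minor beside the sampling error, and that the choice of between-participant SD is a convention. Baseline SD is one reasonable choice among several.

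**Conclusion.** The point holds as an effect-size definition that is badly fixed for its declared purpose. The bias of 6.8% (12 df) or 7.5% (11 df) follows from the sample size and normality; it is small and avoidable.

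The missing link to the ANCOVA matters more. If the ordinary raw form is used, the plan gives up precision and allows sign disagreement at the rates shown above. If the residual SD is used, the bands no longer fit. Both consequences depend on the assumed correlation and on which definition the analysts adopt, and the article settles neither. The ANCOVA estimate, its P value and the hierarchy from creatinine to HDL-C are not affected. The change should be made, but it is not critical to the validity of the primary analysis.

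**What to change.** Replace the Cohen *d* sentence with a definition tied to the primary model:

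- Report the ANCOVA-adjusted group difference in original units with its 95% CI first.
- Then report a standardized effect: that adjusted difference divided by a named between-participant SD (for example the pooled baseline SD, and not the residual SD), multiplied by the Hedges correction (0.936 at 12 df), with its 95% CI.
- Apply the magnitude bands only to this quantity.

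The cost is one sentence and a one-line calculation, with no new data. Stated effect sizes become about 6% smaller (1 − 0.936 = 0.064). Because the article reports the database locked and analyses underway, the definition should be recorded as a dated change, stating whether it was made before any group comparison was seen.
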